### Sample size

The sample size calculation is based on a power calculation for the primary outcome i.e. the Skills and Technique acquisition scale of the heiQ at T1. Previous studies have shown effect sizes (Cohen’s *d*) of similar interventions on the Skills and Technique Acquisition scale of 0.17, 0.50, 0.25, 0.50, 0.31 and 0.59 [49–54]. Based on these previous results, we estimate the effect size of the intervention to be 0.38, which is the average effect size observed in the previous studies. Using an ANCOVA model applied at the patient level, with an adjustment for baseline Skills and Technique Acquisition and treatment group (pre- or post-intervention), 82 patients per group are needed to obtain a power of 80% to detect a significant effect of the intervention, at a two-sided significance level of .05. To account for the effects of adjustment for covariates, dropout and missing data, and contamination, we aim to include 100 patients per group, 200 in total. Note that the ANCOVA model assumed in the power analysis differ slightly from the linear mixed model described for the primary analysis below.

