### Data analysis

Data will be coded with a unique code per patient. The key of these codes will be safeguarded by the coordinating and the principal investigator with a password. No other persons will have access to the key. All data will be kept for 15 years, according to the Dutch Personal Data Protection law. Data will be stored using the data capture applications Gemstracker and Limesurvey. These systems are managed by the Department of Information Management of Erasmus MC and are secured with an individual password for the coordinating and principal investigator.

To assess if randomization has resulted in comparable groups, we will compare patients in the control and in the experimental period at baseline (T0) on characteristics as well as primary and secondary outcomes. Descriptive statistics will be presented as frequencies (%) for categorical variables. Continuous variables will be described as median and interquartile range for non-normally distributed variables and as mean and standard deviation for normally distributed data.

The primary analysis of the study is an initial univariate exploration of the effect of the intervention. Continuous outcomes at T1 between the patients in the control and experimental period will be compared and tested using the Mann-Whitney *U* test for non-normally distributed data and the independent-samples *t* test for normally distributed data. For the BAASIS, a 2 × 2 chi-squared test will be conducted (adherent yes/no × control/experimental group). In univariate analyses, the relationship between patient characteristics (such as age and gender) and medical characteristics (such as organ type and centre) and the outcomes will be assessed.

For the multivariate analyses, linear mixed models analysis will be conducted to account for repeated measures per patient, covariates organ and transplant centre and other significant covariates. All models will be estimated using intention-to-treat analysis incorporating all eligible patients from whom data was obtained. There are three measurement time points (T0, T1 and T2) to be included in these analyses. For missing data in predictor variables, we will use multiple imputation. A *p* value < 0.05 is considered statistically significant.

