We will assess the differences on the primary and secondary outcomes between patients in the control period and versus the experimental period at both T1 and T2 on the outcomes (between-groups comparison). We will also assess the differences on the outcomes between T0–T1 and T0–T2 within the control period and within the experimental period (within-groups comparison). The secondary outcome measure *medication adherence*, which is a dichotomous variable, will be analysed with a generalized estimating equations logistic regression. If the effect of the intervention is found to differ according to organ type then separate explorative multivariate analyses will be conducted to assess the effect per organ.

Among NPs, in an initial univariate analysis, we will compare self-management support skills, using all scales of the SEPSS-36, before and after the experimental period (T0-prior to training and T1-at the end of the implementation period). For non-normally distributed data, we will use the Wilcoxon signed-rank test and the paired samples *t* test in case of normally distributed data.

The video recordings of the NPs will be assessed in blocks of 5 minutes each. Of every recording, a 5-minute clip will be randomly assigned to be observed by two researchers independently. The clips from the control period will be compared with the clips of the experimental period on the needs-thwarting and needs-supporting subscales and tested using the Wilcoxon-signed rank test for non-normally distributed data and the paired samples t-test in case of normally distributed data.

The interviews and qualitative questions in the questionnaire, which will be used to qualitatively evaluate the intervention and the nurse-led care, will be transcribed by at least two researchers independently and analysed thematically [55] using NVivo.

To examine if contamination occurred, we will compare the primary outcome (Skills and Technique Acquisition - heiQ) among control period patients in the contamination phase versus those in the control period not in the contamination phase at T1 and T2. This will be done using an independent samples *t* test. If there is a significant difference, we will control for contamination in the main multivariate analysis.

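### The 82 per group rests on a baseline-adjusted T1 comparison, but no T1 comparison in the analysis section states that adjustment; the cost is 0 to about 12 points of power, depending on how T0 enters the mixed model

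*Protocol article*

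**What the plan says.** Under Sample size, the protocol article powers the heiQ Skills and Technique Acquisition score at T1. The assumed effect is a standardised difference: "we estimate the effect size of the intervention to be 0.38, which is the average effect size observed in the previous studies". The model is given as "Using an ANCOVA model applied at the patient level, with an adjustment for baseline Skills and Technique Acquisition and treatment group (pre- or post-intervention", and the result is that "82 patients per group are needed to obtain a power of 80% to detect a significant effect of the intervention". The test is two-sided with alpha 0.05. The recruitment target is then raised to 100 per group, to cover covariate adjustment, dropout, missing values and contamination. The section closes with a caveat: "Note that the ANCOVA model assumed in the power analysis differ slightly from the linear mixed model described for the primary analysis below".

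Under Data analysis, two T1 comparisons are described.

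- **A univariate comparison** of the two periods at T1 (t test or Mann-Whitney test). This section labels it the primary analysis, although Sample size gives that label to the mixed model. It has no baseline term.
- **A linear mixed model** with repeated measures per patient. Its covariates are organ, centre and any others found significant; the T0 score is not named. On the time points the text says "There are three measurement time points (T0, T1 and T2) to be included in these analyses". The effect is read as control "versus the experimental period at both T1 and T2 on the outcomes (between-groups comparison". Changes from T0 to T1 and from T0 to T2 are also estimated within each period.

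**The concern.** An ANCOVA gains precision because each patient's T1 score is judged against that patient's own T0 score. A mixed model does not gain this merely by including T0. If T0 is one of three responses and each period has its own mean at each visit, the T1 contrast with complete data is the plain difference in T1 means, and the T0 scores add no precision to it.

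Two things are at stake. First, the stated 80% may not belong to the analysis that will be run. This is so even in the protocol's own patient-level framework, before any allowance for departments or calendar time. Second, Study design and randomization says that control and experimental patients are different people, and they are recruited in different periods. A T0 difference between them is therefore possible, and part of it would carry into an unadjusted T1 contrast.

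**Working it through.** **Inputs.** From Sample size: d = 0.38, two-sided alpha 0.05, power 80%, 82 per group calculated, 100 per group recruited. (The six listed effects average 0.387; the plan's 0.38 is used here.) The T0–T1 correlation ρ is not given and is solved for.

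**Step 1: reproduce the 82.** With T1 variance 1, n per group = 2v((1.96 + 0.8416)/0.38)², where v is the variance factor of the contrast.

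- No adjustment, v = 1: n = 108.7, so 109 (110 with the t distribution).
- ANCOVA, v = 1 − ρ². Setting n = 82 gives ρ = √(1 − 82/108.7) ≈ 0.496. With ρ = 0.5, v = 0.75 and n = 0.75 × 108.7 = 81.5, so 82 (83 with t).

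The plan's figure is reproduced, and it depends on the baseline adjustment.

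**Step 2: variance factor of each T1 contrast at ρ = 0.5.** For the mixed model these follow from generalised least squares with three visits and complete data. They are the same under exchangeable and AR(1) correlation.

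- T0 as covariate, or T0 as response with a common T0 mean: 1 − ρ² = 0.75.
- T0 as response with free group means, or the unadjusted T1 t test: 1.
- Difference between periods in T0–T1 change: 2(1 − ρ) = 1.

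**Step 3: power** = Φ(0.38√(n/2)/√v − 1.96).

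| T1 contrast | v | 82 per group | 100 per group |
|---|---|---|---|
| T0 covariate, or common T0 mean | 0.75 | Φ(2.810 − 1.96) = 80.2% | Φ(3.103 − 1.96) = 87.3% |
| Free T0 means, or unadjusted t test | 1 | Φ(2.433 − 1.96) = 68.2% | Φ(2.687 − 1.96) = 76.6% |
| Difference in change | 1 | 68.2% | 76.6% |

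The noncentral t gives 79.8% against 67.7% at 82, and 87.0% against 76.2% at 100. The loss is about 12 points at 82 and 11 at 100. With a common T0 mean it is zero.

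**Step 4: sensitivity to ρ at 82 per group.** Free T0 means give 68.2% at every ρ. The adjusted contrast gives 75.6% at ρ = 0.4, 86.0% at 0.6 and 92.6% at 0.7. The change contrast gives 60.3%, 77.6% and 88.1%. Only ρ near 0.5 agrees with the stated 82 and 80%.

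**Step 5: imbalance at T0.** Suppose the periods differ by 0.2 SD at T0.

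- If the difference decays with ρ = 0.5, it leaves 0.5 × 0.2 = 0.1 SD at T1, about a quarter of the assumed effect (0.1/0.38 = 0.26). The contrast with free means keeps this. T0 adjustment subtracts ρ × 0.2 = 0.1 and leaves none.
- If the difference persists in full, T1 differs by 0.2 SD and T0 adjustment leaves 0.2 − 0.1 = 0.1 SD.

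**The case against.** The strongest reply is that the article does not specify free T0 means. It says that three time points are included, which a model with a common T0 mean also satisfies, and that model is as efficient as ANCOVA. The open-ended covariate clause does not exclude the T0 score either. How T0 enters a mixed model is detail that an analysis plan commonly holds, and the article admits that its two models differ. All of this stands as far as it goes. A reader might infer that the mixed model certainly lacks the adjustment and certainly loses 11 to 12 points; the text does not support that.

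Three further limits also stand.

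- That the T0 scores add no precision is exact only for complete data. With dropout, the T0 scores of patients missing T1 add a little. Organ and centre may recover some precision too, by an amount that the document does not allow one to compute.
- A reader might infer that a T0 imbalance passes in full into the T1 contrast, or that ANCOVA always removes it. Step 5 shows that neither holds in general. Organ and centre would also absorb imbalance due to organ or centre mix.
- ρ = 0.5 is solved back from the 82, not stated.

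What the reply does not meet is that the article goes beyond leaving detail out. It describes covariates, time points and contrasts, and then vouches that the departure from its power model is slight. Free means are the plainer reading: T0 outcomes are to be compared between periods, changes from T0 are estimated within each period, and no common-mean constraint is mentioned. Treating the univariate test as primary offers no way out, since for the unadjusted t test the loss does not depend on any unstated detail.

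**Conclusion.** The point holds in conditional form. The sample size depends on adjusting T1 for T0, and neither T1 comparison described under Data analysis states that adjustment. For the mixed model the cost is between 0 points (T0 means constrained equal) and about 12 points at 82 per group or 11 at 100 (free T0 means). In the latter case power is about 68% and 76%, and even 100 fully analysed patients per group fall short of 80%. The 18 extra patients per group are in any case set aside for covariates, dropout, missing data and contamination.

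These figures assume d = 0.38, a correlation of 0.5, complete data, independent patients and no gain from organ or centre. They are not the power of the stepped-wedge design, since neither they nor the plan's 80% allow for department clustering or calendar time. The description of the model difference as slight is unsupported as written; it would be right only under a constraint that the article does not mention.

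**What to change.** **Data analysis.** Take the primary T1 effect from a mixed model that adjusts for T0, in one of two forms:

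- T1 and T2 as responses, with visit and period-by-visit terms and the patient's T0 score forced in as a covariate, not selected by significance; or
- T0, T1 and T2 as responses, with one common T0 mean for the two periods.

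Report the planned within-period changes from T0 to T1 and T0 to T2 from a separate model or descriptively, because neither form gives them directly with a separate T0 mean per period.

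**Sample size.** Replace the remark that the difference is slight with a statement that the 80% is a patient-level figure, applies only to a T0-adjusted T1 contrast at an assumed T0–T1 correlation of about 0.5, makes no allowance for department clustering or calendar time, and is about 68% at 82 per group without T0 adjustment.

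**Cost.** Wording only. T0 is already collected from patients in both periods, so no extra patients or data are needed. With T0 as a covariate, patients without a T0 score depend on the multiple imputation already planned for predictors. With a common T0 mean, both periods share one estimated baseline. Leaving the contrast unadjusted would instead require 109 to 110 analysed patients per group, or about 133 recruited at the plan's own ratio (109 × 100/82).

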## Methods/design

### Study design and randomization

This multi-centre study in the Netherlands has an unblinded stepped wedge cluster randomized design [32] with pre- (T0) and post-intervention measures after six months (T1), with a follow up after twelve months (T2). The framework of this trial is superiority, whereby we will compare the outcomes between the control and intervention group, and between baseline and follow up data. Seven departments of five University Medical Centres will participate in the study, four kidney transplantation units, one heart transplantation unit, one liver transplantation unit and one lung transplantation unit. The coordinating centre is Erasmus MC, department Nephrology and Transplantation. This department is responsible for coordinating the study, distributing the questionnaires, training of the NPs and the data analysis. A steering committee is present to contribute ideas and to oversee the process.

Given the nature of the programme and the fact that NPs are trained in delivery of the intervention and communication skills, the NPs delivering the intervention cannot be blinded to the group allocation. Therefore, randomization will be performed at the department level. This will be carried out by an independent professional not involved in the study using sealed opaque envelopes. The envelopes with department names and envelopes with start date will be prepared and shuffled by the researcher. The independent professional then randomly chooses the envelopes. All seven participating departments commence the study with standard care i.e. the control period (see Fig. 1) in September 2020. The timing of transition of departments from control to experimental  period is randomized. The first department will be randomized to commence the experimental period in March 2021. During the experimental period, patients receive standard care plus the ZENN intervention. Patients in the control period are different from the experimental period patients, meaning that they will not cross-over.

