### Eligibility criteria

#### Patients

Eligible patients are heart, kidney, liver or lung transplant recipients who have received a transplant in one of the participating centres. The NP will ask patients to participate and hand out the written information on the study. Inclusion criteria are: over 18 years old, between two and thirteen months elapsed after transplantation, sufficient command of the Dutch language and the presence of a functioning graft. Exclusion criteria are cognitive limitations, participating in other lifestyle or self-management promoting programmes which could influence the outcome, and in case of kidney transplant recipients, an expected need for renal replacement therapy within 3 months of inclusion.

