**Patients in the experimental period**				
− What are the differences in patients’ self-management skills between the control and experimental period? − What are the differences in patients’ self-management skills between pre- and post-intervention?	heiQ	X	X	X
− What are the differences in patients’ self-regulation skills in the context of transplantation?	Newly developed self-report instrument	X	X	X
− What is the difference in patients’ medication adherence between patients in the control and experimental period? − What is the difference in patients’ medication adherence between the control and experimental period?	BAASIS	X	X	X
− What is the differences in quality of life after the transplantation between patients in the control and experimental period?	WHOQoL-BREF heiQ	X	X	X
− What is the difference in patients’ experience and appreciation of nurse-led care between the control and experimental period?	Newly developed questions CAHPS		X	
− What is patients’ experience and appreciation of the self-management intervention?	Newly developed questions		X	

**Table 2 Tab2:** Overview of research questions and measures at different time-points—nurse practitioners

Research question	Instrument	T0	T1
− What are the differences in nurses’ self-management support skills between the control and experimental period?	SEPSS-36	X	X
− What are nurses’ experience and appreciation of the self-management intervention?	Semi-structured interview		X
− What is the difference in nurses’ needs-thwarting and needs supporting between the control and experimental period?	COUNSEL-CCE	X	X

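### Uncontrolled baseline-to-follow-up change is written into the superiority framework, although it cannot show that ZENN is better than standard care

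*Protocol article*

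**What the plan says.** Three places in the protocol article bear on this.

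- **Study design and randomization.** The design sentence reads "this trial is superiority, whereby we will compare the outcomes between the control and intervention group, and between baseline and follow up data". The change from baseline therefore stands inside the definition of superiority, on the same footing as the group comparison.
- **Data analysis.** The plan compares outcomes "between patients in the control period and versus the experimental period at both T1 and T2 on the outcomes (between-groups comparison") and then continues: "We will also assess the differences on the outcomes between T0–T1 and T0–T2 within the control period and within the experimental period". The same section sets one significance threshold, p < 0.05, for the analyses in general. It does not say that the within-group comparisons are descriptive.
- **Appendix, Table 1.** For patients in the experimental period a separate research question asks "What are the differences in patients’ self-management skills between pre- and post-intervention". The control-period part of the table has no such question.

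Two further facts matter. Patients enter "between two and thirteen months elapsed after transplantation" and are followed for twelve months. And "Patients in the control period are different from the experimental period patients", so no patient serves as his or her own control across the two conditions.

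**The concern.** The stated aim is to test ZENN in comparison to standard care. A change from T0 to T1 or T2 within the experimental group has no comparator. It is the sum of any ZENN effect and everything else that moves the score over those months:

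- recovery and adjustment after transplantation, which the Introduction itself describes as a time of physical, social and emotional challenge;
- calendar time, in a study that began recruiting in September 2020 and mentions COVID-19 adaptations to both the intervention and the training;
- any regression to the mean, probably the least of the three, since entry is not tied to a heiQ score.

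No test within one group can separate these. Because the design sentence counts such a change towards superiority, a significant pre-post result could be reported as meeting the trial's framework even if the groups did not differ. That is what is at stake: what the trial may conclude, not whether its primary test is valid.

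**Working it through.** **1. The plan's own figure.** The Sample size section gives 82 patients per group for a between-group ANCOVA at T1, with d = 0.38, two-sided 0.05 and 80% power. The baseline-T1 correlation ρ is not stated.

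- Without baseline adjustment: n = 2 × (1.960 + 0.842)² / 0.38² = 15.70 / 0.1444 ≈ 108.7, so 109 per group.
- With ANCOVA, multiply by (1 − ρ²). At ρ = 0.5: 108.7 × 0.75 ≈ 81.5, so 82.

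The figure is reproduced at ρ = 0.5 (power at 82 is 0.802). Correlations of 0.3, 0.4, 0.6 and 0.7 would give 99, 92, 70 and 56. The calculation concerns the group difference only and says nothing about within-group comparisons.

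**2. How often a pre-post comparison is significant when ZENN does nothing.** Inputs:

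- n = 100 per group (Sample size) and two-sided 0.05 (Sample size; p < 0.05 in Data analysis);
- true ZENN effect 0;
- change over time g, in SD units, from causes other than ZENN: assumed, because the documents give no figure;
- T0-T1 correlation ρ: assumed 0.3, 0.5 and 0.7.

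With equal SDs at both times, the SD of the change is √(2(1 − ρ)), which is 1.183, 1.000 and 0.775 for the three correlations. The noncentrality is g × √n / SD of change. For g = 0.2 and ρ = 0.5 it is 0.2 × 10 / 1.000 = 2.0. The probability of significance comes from the noncentral t distribution with 99 degrees of freedom. A time contrast within one group from a mixed model behaves much the same when data are complete.

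| Change over time (SD) | ρ = 0.3 | ρ = 0.5 | ρ = 0.7 |
|---|---|---|---|
| 0 | 5% | 5% | 5% |
| 0.1 | 13% | 17% | 25% |
| 0.2 | 39% | 51% | 73% |
| 0.3 | 71% | 84% | 97% |

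With 82 patients and ρ = 0.5, changes of 0.1, 0.2 and 0.3 SD give 15%, 43% and 77%.

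**3. Reading.** Even at 0.1 SD the probability is well above 5%. These are not errors of the paired comparison, which correctly detects that scores moved. They are errors only if the movement is read as an effect of ZENN.

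**The case against.** The strongest reply is that the trial already rests on between-group evidence. The primary analysis compares control and experimental patients at T1, the sample size is built on that comparison, and the aim is stated against standard care. The within-group comparisons are introduced as additional and cover both groups, so the control group's change will be visible alongside. All of this stands, and it limits the point to additional analyses and to the definition of superiority.

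Some stronger readings are tempting, but the document does not support them.

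- *Aim 2, on sustained change, rests only on pre-post comparisons.* It does not: the between-group comparison is planned at T2 as well as T1. Only an explicit contrast of T2 with T1 is unstated.
- *Separate paired tests are planned for patients.* Paired tests are named for the nurse practitioners only. For patients the comparisons could equally be time contrasts within the mixed model, which includes T0, T1 and T2.
- *Effectiveness will be judged by significance in one group and not in the other.* No such rule is stated. With equal change in both groups that pattern would occur in about 14%, 25% or 13% of trials at 0.1, 0.2 or 0.3 SD (n = 100, ρ = 0.5). But 25% is the most that p(1 − p) can reach, so it is not a typical figure.
- *The between-group comparison is too weak, so within-group p-values will be presented instead.* The text checked here does not show this, and the point does not need it.

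The reply does not remove the wording of the design sentence. It places the baseline comparison inside superiority, and nothing later in the article takes it out or labels it descriptive.

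**Conclusion.** The point holds in a limited form and is worth correcting. A baseline-to-follow-up change cannot support superiority over standard care, yet the article counts it in the superiority framework, applies a general significance threshold without an exception for it, and poses it as a research question for experimental patients. The primary between-group test at T1 and the sample size are untouched, and no stated number is wrong.

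The probabilities of 17%, 51% and 84% rest on an assumed change over time and an assumed correlation of 0.5, with no ZENN effect and all 100 patients observed. The document supplies neither assumption, so they illustrate the size of the risk and do not predict it. The conclusion that such a change has no control does not depend on them.

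**What to change.** 1. In Study design and randomization, delete the last clause of the superiority sentence, so that superiority means the comparison of control and intervention groups only.
2. In Data analysis and Table 1, state that within-group changes are descriptive, reported as estimates with confidence intervals, and are not evidence of effectiveness.
3. Base aim 1 on the between-group difference at T1. Base aim 2 on the already planned between-group difference at T2 and its contrast with T1 (the group-by-time term). Take these from the planned linear mixed model for continuous outcomes, and use the corresponding terms in the planned generalized estimating equations model for medication adherence.
4. Include calendar period and department in these models. In a stepped wedge the experimental patients are recruited later than the control patients, so without a period term the group contrast would itself carry calendar time.

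The cost is wording and a few model terms, with no change to data collection. The period and department terms may widen the confidence interval of the group contrast. The other loss is small: pre-post p-values are no longer available as supporting evidence.

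### Baseline-to-follow-up change within a period is written into the superiority framework and a Table 1 question, but it cannot separate the effect of ZENN from natural change

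*Protocol article*

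**What the plan says.** Four places in the protocol article bear on this.

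- **Study design and randomization.** The superiority framework is explained as "we will compare the outcomes between the control and intervention group, and between baseline and follow up data". The two comparisons stand side by side, and the second is not marked as descriptive.
- **Data analysis.** Control and experimental patients are compared "versus the experimental period at both T1 and T2 on the outcomes (between-groups comparison"). The next sentence adds T0–T1 and T0–T2 differences "within the control period and within the experimental period (within-groups comparison"). The section sets one significance threshold, p < 0.05, and makes no exception for the within-period comparisons.
- **Appendix, Table 1, experimental-period block.** After the question on control versus experimental period, the same cell asks about differences in patients' "self-management skills between pre- and post-intervention". The control-period block has no counterpart.
- **Eligibility criteria, Patients.** Patients enter with "between two and thirteen months elapsed after transplantation".

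The analysis labelled primary is between groups: "Continuous outcomes at T1 between the patients in the control and experimental period will be compared and tested". The sample size is also for the treatment-group effect at T1.

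**The concern.** Superiority here means better than standard care. A change from baseline in patients who all received the intervention has no standard-care comparator, so it cannot show this. It is the sum of any ZENN effect, adaptation that would have occurred anyway, the effect of completing the same questionnaire again, and regression to the mean. The article's Introduction describes physical, social and emotional challenges after transplantation, so some change under standard care is plausible.

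Running the same comparison in the control period does not repair this if the two results are read side by side. A p value below 0.05 in one period and above it in the other can arise when the true changes are identical. The difference between the two changes has to be estimated and tested directly.

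At stake is what the trial may conclude. As worded, a significant experimental-period change answers the Table 1 pre/post question and falls within the stated superiority framework, even if the between-group comparison shows nothing.

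**Working it through.** **1. What the plan's own figure supports.** Inputs from Sample size: d = 0.38, 80% power, two-sided alpha 0.05, ANCOVA adjusted for baseline, 82 per group. The unadjusted number is 2 × ((1.960 + 0.842)/0.38)² = 108.7 per group. ANCOVA multiplies this by (1 − r²), where r is the T0–T1 correlation. The article does not state r. With r = 0.5, 108.7 × 0.75 = 81.5, which rounds up to 82. The stated figure is reproduced (r = 0.4 gives 92, r = 0.6 gives 70). It is a between-group calculation, and no sample-size argument is given for the within-period comparisons.

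**2. When patients are measured.** Entry is 2–13 months after transplantation. T1 falls at 2 + 6 = 8 to 13 + 6 = 19 months, and T2 at 2 + 12 = 14 to 13 + 12 = 25 months.

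**3. How often a within-period test is significant when ZENN does nothing.** Assumptions, none of them in the article: zero ZENN effect; natural T0–T1 change δ of 0.1, 0.2 or 0.3 SD, equal in both periods; r = 0.5 or 0.6; a paired t test at two-sided 0.05. For n, I use 82 (required) and 100 (planned) per period.

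- SD of change = √(2(1 − r)), which is 1.000 at r = 0.5 and 0.894 at r = 0.6.
- Noncentrality = δ√n / SD of change. Example: δ = 0.2, n = 100, r = 0.5 gives 0.2 × 10 / 1 = 2.00. Against a critical t of 1.984, the probability of significance is 51%.
- With equal true changes and independent periods, the probability that the experimental period is significant and the control period is not is p(1 − p).

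| Natural change | n = 82, r = 0.5 | n = 82, r = 0.6 | n = 100, r = 0.5 | n = 100, r = 0.6 | Experimental yes, control no |
|---|---|---|---|---|---|
| 0 | 5% | 5% | 5% | 5% | about 5% |
| 0.1 SD | 15% | 17% | 17% | 20% | 12–16% |
| 0.2 SD | 43% | 52% | 51% | 60% | 24–25% |
| 0.3 SD | 77% | 85% | 84% | 91% | 8–18% |

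The last column falls again at 0.3 SD because both periods then tend to be significant.

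**4. The between-group test under the same conditions.** In 20,000 simulated trials (n = 100 per period, r = 0.5, no ZENN effect), the between-group t test at T1 was significant in about 5% for natural changes of 0, 0.2, 0.3 and 0.38 SD. A change common to both periods cancels in that contrast. The simulation treats patients as independent and has no clustering or calendar trend. It shows the contrast between the two kinds of comparison. It does not give the error rate of the between-group test in this stepped-wedge design.

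**The case against.** The strongest reply is that the plan already puts the between-group comparison first. The aim is effectiveness in comparison to standard care, the sample size and the analysis labelled primary are between groups, and the within-period comparison is introduced as an addition and is run in the control period too, so natural change would be visible there. No paired test is named for patients; the within-period differences may be contrasts from the planned mixed model. The Table 1 question could not be worded for control patients, who receive no intervention. How such changes are labelled is often left to an analysis plan.

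Much of this stands, and it rules out the stronger reading. A reader might infer that natural recovery in the first post-transplant year will be reported as the ZENN effect. The article does not say so. Nowhere does it state that a within-period change will be presented as the intervention effect, nor does it propose inferring an effect from significance in one period only. It gives no size or direction for natural change. Follow-up also runs past the first year for many patients at T1 and for all of them at T2.

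What does not fall away is the text itself. The framework sentence puts the baseline comparison inside superiority, and Table 1 poses a question that, as worded, an uncontrolled change would answer. These are statements in the article, not details deferred to another document. Using mixed-model contrasts instead of paired tests does not change the point, because a within-period contrast still has no comparator.

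**Conclusion.** The point holds as a fault in the stated framework and in one research question; the primary comparison is not affected. Within-period comparisons cannot support superiority, and as written they could be used to claim an effect that the between-period comparison does not show.

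The size depends wholly on how much patients change under standard care, which the article does not give. Under the assumptions above, the chance of a significant experimental-period change with an ineffective intervention runs from the nominal 5% with no natural change to 77–91% at 0.3 SD. These percentages are the power to detect a real change over time. They become error rates for the claim that ZENN works only if someone draws that inference, and the present wording leaves it open. The correction is worth making because it governs what the trial may conclude and costs almost nothing.

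**What to change.** - **Study design and randomization:** rest superiority on the contrast between control and experimental period only, and remove the baseline-to-follow-up comparison from that sentence.
- **Data analysis:** state that T0–T1 and T0–T2 changes within each period are descriptive, reported as estimates with 95% confidence intervals, and are not evidence of effectiveness. The label matters most; leaving out the p values is partly a matter of reporting style.
- **Appendix, Table 1:** answer the pre/post question by the between-period difference in T0–T1 and T0–T2 change, taken as the period-by-time contrast from the linear mixed model already planned for T0, T1 and T2.

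Cost: wording only, with the same data and the same model. The downside is fewer within-period significance statements to report.
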